### Cost-effectiveness analysis

We will perform an incremental cost-effectiveness analysis from the payer perspective. Direct intervention costs (labor, material and supplies, and contracted services costs) associated with delivering the intervention over the one-year period will be collected and follow a cost collection approach described elsewhere [29]. The incremental costs of the intervention will need to account for any vision services received by the usual care group and any differences in costs for non-vision related services that may be an indirect result of the intervention. Information will be collected for any participants who fall or are hospitalized, transferred to high care or die. Aggregating these costs over the six-month period and adding them to the direct costs of the ROC intervention group, will allow the total medical costs for the intervention and the usual group to be quantified. The incremental cost-effectiveness ratio (ICER) will be calculated using the estimated mean difference in effect (EQ-5D-3L) and the estimated mean difference in costs between the intervention and the control groups. The ICER indicates the average incremental cost to gain one additional quality-adjusted life year (QALY). Cost data are likely to be skewed. Therefore, using non-parametric bootstrapping, 1000 replicates [30] will be generated to estimate the 95% confidence intervals around the ICER. A cost-effectiveness acceptability curve (CEAC) [31] will be used to show the probability that the intervention is cost-effective for a range of monetary values that a decision maker might be willing to pay for a unit change in QALYs. Cost-effectiveness will initially be quantified assuming that QALYs are only sustained for one year, but an assessment will also be made based on the assumption that they continue to accrue each year for the expected remaining life years in the study sample. Additional one-way (and n-way) deterministic sensitivity analyses will be performed to examine the effect of changing one (or n) of the model parameters.

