#### Low vision rehabilitation

Participants with VA < 6/12 (0.3 LogMAR) not correctable by either refraction or cataract surgery will be eligible for the low vision rehabilitation pathway. An ACO optometrist will undertake an initial comprehensive vision and ophthalmic review and provide low vision aids where appropriate at no cost. The type of low vision aids provided will be determined by the level of VI, the level of magnification required to perform desired tasks and the participant’s ability to use aids of different designs. Detailed demonstration, training, and instruction on aids will be given to the participant. Details of this examination will be forwarded with referral to the nearest Vision Australia center, Australia’s leading provider of blindness and low vision rehabilitation services, where an appointment will be scheduled within eight weeks. At this appointment, a Vision Australia Occupational Therapist will conduct a “Techniques for Daily Living” session with the participant, focusing on areas of difficulty and concern. Each session will be adapted to the individual circumstances of the resident, but be based around application of the following techniques:*Lighting:* general and/or task lighting;*Size:* bring things closer, make them larger, and vary the use of prescribed magnification;*Contrast:* increase the contrast between the foreground and the background;*Senses:* touch, scent, sound, and taste;*Marking:* tactile and/or contrast colored marking;*Labeling:* large print, Braille, or audio labels;*Organization:* different systems for organizing belongings;*Equipment:* everyday devices and/or functional use of low vision aids.

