### Statistical analysis

The primary and secondary outcomes will be assessed using an intention-to-treat analysis applied to individual participants and repeated using the per-protocol sample (only participants who complete the clinical trial including the second assessment). To compare the effectiveness of ROC with usual care, presenting and best corrected near and distance VA (primary outcome) at the two- and six-month follow-ups will be analyzed and the differences from baseline VA will be used to investigate changes. The near and distance VA change is expected to be normally distributed and analysis of covariance will be used to compare the difference, adjusting for baseline values. Effect sizes for both groups will be calculated using Cohen’s d coefficient [27]. To determine the effectiveness of ROC on secondary outcomes, a Multivariable General Linear Model will be used to compare differences at two and six months from baseline on the IVI-RC, EQ-5D-3L and CSDD. If the EQ-5D-3L data are skewed, a multivariable quantile regression model will be used. Falls data will be compared across intervention and usual care groups at six months using a negative binomial regression if the data are over-dispersed. Changes in mobility will be analyzed using Mann–Whitney U tests. The difference in utilization of distance and near vision glasses and low vision aids between the treatment groups will be compared using the Chi-squared test and the utilization time will be compared using Student’s t-test or non-parametric test if appropriate. A multi-level model with a random intercept parameter will be utilized to account for within cluster correlations. All analyses will be performed using STATA version 15 (StataCorp. 2017. Stata Statistical Software: Release 15. StataCorp LLC, College Station, TX, USA).

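### The ICER denominator is a mean EQ-5D-3L difference carried for one year; it equals a QALY gain only if the utility gain is immediate and constant, and it leaves out time lost to death

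*Protocol article*

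**What the plan says.** All of the economic rule is in the protocol article under Cost-effectiveness analysis. The ICER "will be calculated using the estimated mean difference in effect (EQ-5D-3L) and the estimated mean difference in costs" between the arms. The following sentence gives its meaning: "The ICER indicates the average incremental cost to gain one additional quality-adjusted life year (QALY". The duration comes later in the same paragraph: "Cost-effectiveness will initially be quantified assuming that QALYs are only sustained for one year". A second analysis assumes instead that "they continue to accrue each year for the expected remaining life years in the study sample".

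On measurement, the section on person-centered outcomes says that EQ-5D-3L responses can be converted to utilities for the economic analyses. Under Statistical analysis, a general linear model will "compare differences at two and six months from baseline on the IVI-RC, EQ-5D-3L and CSDD". Utilities are therefore planned at baseline, two months and six months, and none is planned later. The economic section does not name the visit that supplies the difference, and no step combines the visits over time.

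Two other places bear on the point. In the low vision pathway, the resident is referred to a rehabilitation center "where an appointment will be scheduled within eight weeks". The Sample size section allows for about 25% loss to follow-up, mostly from deaths.

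**The concern.** A utility is a level at a moment. A QALY is that level multiplied by the time lived at it. A mean difference in EQ-5D-3L becomes a QALY gain only when a duration is attached. Attaching one year to a single difference treats the gain as present in full from the start and unchanged throughout.

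The plan's own timetable makes immediate benefit doubtful for some residents. The rehabilitation session may fall close to the two-month visit, and cataract surgery and ophthalmic treatment come only after referral and assessment. The two-month utility would show how fast the gain builds, but the stated rule does not use it.

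A difference in levels multiplied by a fixed duration also gives no place to time not lived. That matters in a population where deaths are expected to account for most of a 25% loss.

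At stake is the denominator of the main economic result. It feeds the ICER and the acceptability curve, and the article intends the trial's findings for policymakers.

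**Working it through.** The article gives no utility difference, QALY gain or ICER, so there is no stated figure to reproduce. Results are expressed per unit of D, the between-arm utility difference at six months.

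Inputs from the article: utilities at 0, 2 and 6 months, and a base-case duration of one year.

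Assumptions, because the article does not give them:
- no between-arm difference at baseline;
- a difference of f × D at two months;
- straight lines between visits;
- the month-6 difference held to month 12;
- the year counted from baseline.

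Area over the observed six months:

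A6 = (0 + fD)/2 × 2/12 + (fD + D)/2 × 4/12

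Area over one year:

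A12 = A6 + D × 6/12

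Denominator on the literal reading: D × 1 year = 1.00 D. The overstatement of QALYs is 1.00 D / A12.

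| Time course | A6 | A12 | 1.00 D / A12 |
|---|---|---|---|
| Immediate and constant | 0.500 D | 1.000 D | 1.00 |
| Full by month 2 (f = 1) | 0.083 D + 0.333 D = 0.417 D | 0.917 D | 1.09 |
| Half by month 2 (f = 0.5) | 0.042 D + 0.250 D = 0.292 D | 0.792 D | 1.26 |
| None by month 2 (f = 0) | 0 + 0.167 D = 0.167 D | 0.667 D | 1.50 |

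For a given cost difference the ICER is too low by the same factor.

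A fading gain goes the other way. Take a difference of 1 at two months and 0.5 at six months:
- A6 = 0.5 × 2/12 + 0.75 × 4/12 = 0.333
- A12 = 0.333 + 0.5 × 0.5 = 0.583
- the literal denominator is 0.5, and 0.5/0.583 = 0.86, so QALYs are understated.

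Deaths are not in these ratios. The article gives no numbers by arm or by time, so their effect cannot be sized from it.

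**The case against.** The strongest reply is that the rule criticised is partly inferred. The parenthesis in the ICER sentence may only name the instrument, as shorthand for QALYs derived from it. No visit is named, and nothing says that the year begins at baseline. A journal article may leave the QALY formula to the full protocol or analysis plan. This stands in part: the single visit and the baseline start are readings of the text, not statements in it. But the shorthand reading fits poorly with the rest of the paragraph. A gain that is carried for one year, or that goes on accruing every year, describes a level held over time and not an area already accumulated. The article states a denominator, so this is more than an omitted detail.

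A reader might go further and infer that the ratio is not a cost per QALY at all, and so cannot be set against a willingness to pay per QALY. The documents do not support that. A utility difference multiplied by the stated one year has QALY units, so what remains is an approximation that depends on the time course.

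A reader might also compare the six-month area with a constant gain over six months (0.50 D) and quote overstatements of 0.50/0.417 = 1.2, 0.50/0.292 = 1.7 and 0.50/0.167 = 3.0 times. Those ratios belong to a six-month horizon, whereas the base case in this section is one year.

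The evidence for delay is limited too. The eight-week figure is an upper limit for one session in one of four pathways. The optometrist supplies low vision aids, with training, before that session, and spectacles are provided through the study. The case of no gain by two months is therefore an extreme.

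**Conclusion.** The point holds in limited form. As written, the denominator is a QALY gain only for an immediate and constant utility effect, and it makes no allowance for time lost to death. For a gradual gain on the one-year base case, QALYs are overstated about 1.09 to 1.50 times. The factor is 1.00 if the gain is immediate and below 1 if the gain fades (0.86 in the example). These figures rest on the assumptions listed with the calculation, above all that the six-month difference is the one used and that the year runs from baseline.

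It would be tempting to conclude that the ICER must come out too favourable. The documents give no time course for EQ-5D-3L, so neither direction nor size is fixed. That uncertainty is itself a reason to specify a method that uses the observed path.

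The mixed cost windows in the same section are a separate matter. Direct intervention costs "associated with delivering the intervention over the one-year period will be collected", while the other costs are handled by "Aggregating these costs over the six-month period and adding them to the direct costs of the ROC intervention group". Aligning those windows would not remove the onset problem, and correcting the onset would not align the windows.

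**What to change.** In Cost-effectiveness analysis, replace the EQ-5D-3L difference as the stated effect with a QALY difference defined as follows:

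- compute each resident's QALYs as the area under the baseline, two-month and six-month utilities, with utility zero from the date of death;
- estimate the between-arm difference in these QALYs with adjustment for baseline utility;
- use that difference as the denominator of the ICER and in the acceptability curve;
- present any extension to one year or to remaining life years separately, labelled as extrapolation beyond the last utility measurement at six months.

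The utilities are already planned, and the section already provides for information on residents who die. The change needs new analysis wording and slightly more analysis work. The price is that the ICER may be less favourable if the gain builds slowly.

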### Participant flow

All prospective participants who sign a study consent form will undergo a screening examination. When inclusion and exclusion criteria are met, the participant will be invited to complete a pre-intervention face-to-face baseline assessment with a research assistant. Following the baseline assessment, participants will receive the ROC intervention or usual care. All participants will be invited to complete follow-up assessments at two and six months after baseline visits.

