#### Person-centered outcomes (secondary)

Mobility will be assessed using the Aged Care Funding Instrument (ACFI) [20] module 2 developed by the Department of Health and Ageing. This component of the ACFI relates to the participant’s usual day-to-day assessed care needs with regard to mobility. Mean mobility scores will be compared between groups. ACFI data will be collected regularly by residential care facility staff.

Vision-specific QoL will be measured using the Impact of Vision Impairment for Residential Care (IVI-RC). The IVI-RC is a 28-item questionnaire developed to measure the impact of vision impairment on activity limitation and emotional wellbeing, and has been adapted specifically to the aged care setting by the study team from the original 28-item IVI questionnaire [21, 22].

Depressive symptoms will be determined using the Cornell Scale for Depression in Dementia (CSDD) [23]. This measure was chosen due to its suitability for use with individuals with moderate cognitive functioning. The interviews focus on depressive symptoms and signs occurring during the week before the interview. The final ratings of the CSDD represent the rater’s clinical impression. Each item is rated for severity on a scale of 0–2 (0 = absent, 1 = mild or intermittent, 2 = severe). The item scores are added together. Scores of 0–8, 9–13, 14–18, and 19–38 indicate no or minimal, mild, moderate, and major depressive symptoms [24].

Regarding falls rate, residential care settings have an incident reporting system (which varies from paper based to computerized systems) where any incident including falls will be recorded. Falls data will be retrieved from incident reporting systems in the participating residential care facilities and the proportion of falls will be compared between groups.

Health-related QoL will be assessed using the five-dimension EuroQoL (EQ-5D-3L) [25], a descriptive system that covers five dimensions (Mobility, Self-care, Usual Activities, Pain/Discomfort, and Anxiety/Depression). The EQ-5D-3L raw data can be converted to utilities, which will be used for our economic analyses.

With regard to utilization of visual devices (distance and near vision glasses; low vision aids), at the two- and six-month follow-up visits, participants in the intervention arm who have been prescribed spectacles or low vision aids, will be asked to self-report on how often the device has been used during the week, for how long it was used, and for what tasks.

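### The ICER's EQ-5D-3L effect is not defined as baseline-adjusted or tied to the EQ-5D-3L model; regressing QALYs on baseline utility would be a free improvement

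*Protocol article*

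**What the plan says.** Under Cost-effectiveness analysis, the ICER is "calculated using the estimated mean difference in effect (EQ-5D-3L) and the estimated mean difference in costs between the intervention and the control groups" and is read as cost per QALY. Uncertainty comes from 1000 bootstrap replicates and an acceptability curve. On the horizon: "Cost-effectiveness will initially be quantified assuming that QALYs are only sustained for one year", with a further assessment in which gains go on accruing over remaining life years. The section names no baseline utility covariate. It does not say whether the effect is a follow-up value, a change from baseline or an area under the curve.

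Under Person-centered outcomes: "The EQ-5D-3L raw data can be converted to utilities, which will be used for our economic analyses".

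Under Statistical analysis, "a Multivariable General Linear Model will be used to compare differences at two and six months from baseline on the IVI-RC, EQ-5D-3L and CSDD". Skewed EQ-5D-3L data are to be handled by quantile regression instead, and a random intercept is to account for clustering. Explicit baseline adjustment is written only for near and distance visual acuity: "analysis of covariance will be used to compare the difference, adjusting for baseline values".

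Under Participant flow, eligible residents are "invited to complete a pre-intervention face-to-face baseline assessment with a research assistant", so a baseline utility is available. Under Randomization, facilities are the allocated units and the strata are facility size and region.

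**The concern.** A resident's utility at two and six months is correlated with utility at baseline. If the arms happen to start apart, part of that gap persists in the follow-up values. An area under the curve would also contain the gap directly, through its first point. Allocation is by facility, only 38 facilities are allocated, and the strata do not include health status, so some gap is to be expected.

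The QALY difference is the denominator of the ICER. The plan then holds it for one year and over remaining life, which scales any artefact with it. Bootstrapping does not remove the artefact, because the replicates centre on the observed difference, imbalance included.

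The EQ-5D-3L model under Statistical analysis does not clearly settle the matter. The economic section does not refer to it. If skewness triggers quantile regression, that model no longer yields the mean difference that the ICER needs.

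**Working it through.** **The plan's own figure.** The documents give no utility SD, QALY or ICER value. The only related figure is enrolment: 38 per arm gives 76; 76 × 3.5 = 266; 266 / (0.90 × 0.75) = 394.07, rounded up to 395. It reproduces and is not in dispute.

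**Inputs from the protocol.** 395 enrolled, 25% lost to follow-up, 38 facilities, 1:1 allocation.

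**Inputs that are assumptions.** Utility SD 0.20–0.35, equal at baseline and follow-up. Correlation rho 0.5–0.7 between baseline and each follow-up utility. Utility ICC 0.05, borrowed from the sample size section, where it serves the visual acuity calculation.

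**Step 1: chance baseline gap between arms.**
- Analysed: 395 × 0.75 = 296, or 148 per arm and 7.8 per facility.
- Design effect: 1 + (7.8 − 1) × 0.05 = 1.34.
- SE of gap = SD × sqrt(2 × 1.34 / 148) = 0.135 × SD, which is 0.027 at SD 0.20 and 0.047 at SD 0.35.
- Typical (median absolute) gap = 0.6745 × SE = 0.018 to 0.032.
- 95% limit = 1.96 × SE = 0.053 to 0.092.
- Sensitivity: with all 395 (10.4 per facility, design effect 1.47), SE = SD × sqrt(4 × 1.47 / 395) = 0.122 × SD = 0.024 to 0.043.

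**Step 2: what the gap does to the QALY difference under each reading of the effect.**
- Raw follow-up utility: + rho × gap × years.
- Area under the curve over 0, 2 and 6 months (trapezoid weights 1/12, 1/4 and 1/6 year): + (0.083 + 0.417 × rho) × gap, that is 0.292 × gap at rho 0.5 and 0.375 × gap at rho 0.7.
- Change from baseline: − (1 − rho) × gap × years.

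| Reading | Direction | Typical gap | Gap at 95% limit |
|---|---|---|---|
| Raw follow-up, six months | same as gap | 0.005–0.011 | 0.013–0.032 |
| Raw follow-up, held one year | same as gap | 0.009–0.022 | 0.026–0.065 |
| Area under the curve, six months | same as gap | 0.005–0.012 | 0.015–0.035 |
| Change score, six months | opposite | 0.003–0.008 | 0.008–0.023 |
| Change score, held one year | opposite | 0.005–0.016 | 0.016–0.046 |

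**Step 3: precision.** Relative to a raw follow-up utility, baseline regression cuts the variance by rho², or 25% to 49%. Relative to a change score, the ratio is (1 − rho²) / (2 × (1 − rho)) = (1 + rho) / 2, a cut of 25% at rho 0.5 and 15% at rho 0.7. Both take rho to be the same within and between facilities.

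**The case against.** The strongest reply is that the economic section is silent, which is not the same as choosing an unadjusted comparison. An estimated mean difference may be model-based, and the only EQ-5D-3L analysis described works with differences from baseline. A condensed article may also leave regression covariates to an analysis plan that is not shown.

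Much of this stands. A reader might infer that the plan commits to an unadjusted ICER, or that a baseline gap will be counted as QALYs gained or lost. The text supports neither. On the change-score reading the gap is subtracted and the residual error has the opposite sign. Area under the curve is one possible construction and is not named in the protocol. Nor is the planned estimator biased: over repeated randomisations, chance imbalance averages out. A claim that the gap could decide the sign of the ICER is also unsupported, because the documents give no expected QALY difference to set it against.

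The reply does not remove the point. Each of the three readings leaves some of the gap in the result, and the quantile regression fallback cannot supply a mean difference. Regression on baseline utility improves all three, so the recommendation does not depend on which reading was meant.

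**Conclusion.** The point holds as a free improvement to a secondary, economic analysis; it does not show an invalid method. The protocol leaves the ICER's EQ-5D-3L effect undefined with respect to baseline and unlinked to its own EQ-5D-3L model. The consequence is lost accuracy given the realised imbalance, and lost precision. Under the assumed inputs the error from a typical gap is below or near 0.01 QALY over six months, about three times that at the 95% limit, and twice as large for a difference held for one year instead of six months. The true size cannot be computed from the documents, since utility SD, rho and the utility ICC are not given.

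**What to change.** In Cost-effectiveness analysis, state how each resident's QALYs are built. Then take the QALY difference from a regression of those QALYs on arm and baseline EQ-5D-3L utility, with the facility random intercept already planned under Statistical analysis. Use this adjusted mean difference in the ICER, in every bootstrap replicate and in the acceptability curve. State that it remains a mean difference even if the clinical EQ-5D-3L comparison moves to quantile regression.

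The cost is a sentence or two of wording and one more model step inside the bootstrap. No new data are needed.

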To date, no study has evaluated the impact of providing comprehensive eye care services to individuals with a broad spectrum of ophthalmic conditions and residing in aged care facilities. Therefore, we will implement a prospective, customized, multicentered, and cluster randomized controlled trial (RCT) to evaluate the clinical, person-centered, and cost-effectiveness of a new model of eye care. We will compare the effectiveness of Residential Ocular Care (ROC) with usual care on improving presenting and best corrected near and distance vision (primary outcome) at the two- and six-month follow-up visits. Secondary outcomes will assess the effectiveness of ROC on improving vision-specific QoL, daily functioning, health-related QoL, depressive symptoms, rate of falls, and eye care utilization, compared to the usual care group at the two- and six-month visits, after baseline, and quantify the cost-effectiveness of ROC at six months after baseline.

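### The base-case ICER pairs one-year QALYs and one-year intervention costs with six-month downstream costs, and no named analysis answers the six-month objective

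*Protocol article*

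**What the plan says.** The last paragraph of the Background says the trial will "quantify the cost-effectiveness of ROC at six months after baseline". Data collection fits that aim. Under Participant flow, "All participants will be invited to complete follow-up assessments at two and six months after baseline visits", and the Statistical analysis section will "compare differences at two and six months from baseline on the IVI-RC, EQ-5D-3L and CSDD", so utilities are available at baseline, month 2 and month 6 and at no later time.

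The Cost-effectiveness analysis section uses three periods for one ratio:

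- Direct intervention costs: those "associated with delivering the intervention over the one-year period will be collected". The article does not define this year further.
- Costs linked to falls, hospital stays, moves to high care and deaths: "Aggregating these costs over the six-month period and adding them to the direct costs of the ROC intervention group".
- Effects: "Cost-effectiveness will initially be quantified assuming that QALYs are only sustained for one year". As the alternative, "an assessment will also be made based on the assumption that they continue to accrue each year" over remaining life expectancy.

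One-way and n-way deterministic sensitivity analyses are announced, but the parameters to be varied are not listed and a six-month horizon is not among the analyses named.

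**The concern.** An ICER is interpretable only if its numerator and denominator cover the same period. Followed as written, the base case credits QALYs in months 6 to 12 that nobody measures, and leaves out the downstream costs of those same months. The bootstrap interval and the acceptability curve would be built on the same mixed ratio.

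The Background also promises a six-month answer. The Cost-effectiveness analysis section goes from a one-year assumption directly to a remaining-lifetime one. The only result supported entirely by observed data is therefore not among the analyses named. Economic effectiveness is one of the trial's stated aims, and the findings are to go to policymakers, so the ratio is likely to be used.

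**Working it through.** The article states no cost, utility difference, QALY gain or ICER, so there is no figure to reproduce. The check asks how far the horizons can move the result.

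**Step 1: QALYs.** Let dU be the between-group utility difference once established. QALY gain is the area under the difference curve, in years. The three trajectories are assumptions.

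| Trajectory of the gain | To month 6 | To month 12, held | Ratio | To month 12, waning linearly to zero | Ratio |
|---|---|---|---|---|---|
| Constant from baseline | 6/12 = 0.500 dU | 12/12 = 1.000 dU | 2.0 | (6 + 3)/12 = 0.750 dU | 1.5 |
| Linear rise to month 2, then flat | (1 + 4)/12 = 0.417 dU | (1 + 10)/12 = 0.917 dU | 2.2 | (5 + 3)/12 = 0.667 dU | 1.6 |
| Linear rise to month 6 | 3/12 = 0.250 dU | (3 + 6)/12 = 0.750 dU | 3.0 | (3 + 3)/12 = 0.500 dU | 2.0 |

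Relative to the six-month objective, the one-year QALY figure is therefore 2 to 3 times as large if the gain is held, and 1.5 to 2 times if it wanes to zero by month 12. The ratio is 1.0 only if the gain disappears at month 6, which is not what the plan assumes.

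**Step 2: the ICER.** Set direct intervention cost over the year to 1. Let f be the share of it falling in the first six months, and d the net between-group difference in downstream cost over six months as a multiple of direct cost. Take the constant gain, in units of dU:

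- Mixed ICER, as written: (1 + d)/1.0
- All at six months: (f + d)/0.5
- All at twelve months, downstream costs continuing at the same rate: (1 + 2d)/1.0

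The ratio of six-month to mixed ICER is 2(f + d)/(1 + d). The ratio of twelve-month to mixed ICER is (1 + 2d)/(1 + d). A ratio above 1 means the mixed ICER is too favourable to ROC; below 1, too unfavourable. The values of f and d are assumptions.

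| d | Six-month/mixed, f = 1 | f = 0.75 | f = 0.5 | Twelve-month/mixed |
|---|---|---|---|---|
| -0.25 | 2.0 | 1.33 | 0.67 | 0.67 |
| 0 | 2.0 | 1.5 | 1.0 | 1.0 |
| 0.25 | 2.0 | 1.6 | 1.2 | 1.2 |
| 0.5 | 2.0 | 1.67 | 1.33 | 1.33 |
| 1.0 | 2.0 | 1.75 | 1.5 | 1.5 |

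With f = 0.5 and d = 0, the mixed ratio agrees with both consistent ones. With f = 1, the six-month ICER is twice the mixed one whatever d is. If ROC saves downstream costs (d = -0.25) and one year is the intended horizon, the mixed ICER is too unfavourable to ROC.

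**The case against.** The strongest defence is that one year is openly labelled an assumption, that direct intervention costs cover the same year, and that further scenarios are planned. Spectacles and cataract surgery can plausibly help beyond six months, so stopping the benefit there while charging their full cost could bias against ROC. This is a fair argument against treating six months as the only valid horizon. It does not bring the downstream costs into line with the QALYs, and it does not supply the six-month result the Background promises.

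Three stronger readings are tempting, and the document does not support them:

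- *The ICER is too favourable by about a factor of two.* This needs a constant effect, all direct cost incurred by month 6, and six months as the comparator. The article gives neither costs nor their timing. The authors expect a beneficial effect on falls; if that lowers downstream costs, cutting those costs off at six months can work against ROC.
- *The raw EQ-5D-3L difference will be used as if it were QALYs.* The section writes the effect term in shorthand but expresses the ICER per QALY, and the conversion may be set out in the full protocol, which is not shown.
- *About 44% of participants would be dead or lost by one year.* The Sample size section allows about 25% loss, mostly deaths, for planning. Doubling the period at constant hazard (1 - 0.75 × 0.75 = 0.4375) extrapolates attrition of all kinds; it is not a mortality estimate.

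**Conclusion.** The point holds as an internal inconsistency in a stated rule. One ratio draws on a one-year period for direct costs and QALYs and a six-month period for downstream costs, while the objective and the data end at six months. Months 6 to 12 of QALY gain are extrapolated without matching downstream costs, and no named analysis answers the six-month question.

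The overstatement of QALYs in Step 1 is relative to the six-month objective and rests on the assumed trajectories. The net bias in the ICER has no determinable size or direction: the tabulated scenarios run from 0.67 to 2.0, and which applies depends on cost timing and on the sign of the downstream cost difference. Severity is moderate. The vision outcomes, the sample size and the data collection are unaffected.

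**What to change.** Reconcile the Background objective with the Cost-effectiveness analysis section, and use one horizon for every cost component and for QALYs in any given ratio.

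- Report the within-trial six-month result. Take QALYs as the area under the baseline, two-month and six-month EQ-5D-3L utilities, count utility as zero from death, and adjust for baseline utility. Restrict all costs to the same six months.
- Show one-year and remaining-life persistence as scenarios, each with downstream costs and mortality extended over the same horizon as the benefit, and include a waning variant alongside the sustained one.

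The six-month analysis uses data already planned for collection, so the cost is rewording and a little analysis work; the scenarios need explicit assumptions on later costs and survival. The downside is that a six-month result may understate lasting benefit from spectacles or surgery, which the scenarios would show.
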